### Concealment mechanism {16b}

The allocation sequence was determined by our IT system developer and was implemented in a web application for managing databases (REDCap). One of its features was used to conceal the allocation until a member of the research team assigned a school to its condition by clicking a button for randomization. As this was done by a person other than the system developer, this process ensured that our research group could not influence the allocation of the schools to the two groups. The order in which the schools were randomized depended on the order in which they decided to participate in the program. Randomization took place as soon as the research group received a signed participation agreement from the school. For organizational reasons, randomization took place before baseline. But only principals and core teams were informed about their group affiliation by the research team and were instructed not to disclose their allocation to their teachers or pupils to avoid influences on pupils’ survey responses.

### Implementation {16c}

As mentioned above, the allocation sequence was generated by our IT system developer. Schools were enrolled and assigned to the IG or CG by different members of the research team.

## Assignment of interventions: blinding

### Who will be blinded {17a}

Schools could not be blinded due to the different natures of the IG as opposed to the CG, i.e. immediate as opposed to delayed implementation of a prevention program. Blinding of the researchers is non-applicable, since they are responsible for the program implementation, and data collection relies on online self-reports only. The data analysts will be blinded to group allocation (dummy coded) when conducting the statistical analyses.

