#### Third objective

To get insight into the effectiveness of specific components of the program, short surveys for teachers will be conducted at T1 and T2. Furthermore, the use of the eLearning platform is recorded continuously (i.e. the proportion of completed eLearning units).

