### Procedure for unblinding if needed {17b}

Since only data analysts are blinded, unblinding is not needed.

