In secondary schools, pupils who agree to participate in the accompanying research also fill in:Attributions for Victimization Experiences Measure ( [37, 38]; 17 items): Cronbach’s alpha = 0.71–0.80 for the subscalesInventory of Callous-Unemotional Traits—Youth Version (ICU; [39]; 24 items): Cronbach’s alpha = 0.77

All measures are well tested standard instruments and have previously been used in adolescent samples.

In addition to the pupil survey, the evaluation of the program relies on documentation of the actual program components implemented at each school through an annual teacher survey. For this purpose, teachers receive an invitation to an anonymous online survey (T1: only IG; T2: IG and CG), taking a maximum of 5 min to answer. In the questionnaire, all teachers are asked to estimate the workload and the benefit of the program and get the opportunity to give feedback to the program. Class teachers are additionally asked about the amount of eLearning units, class meetings, and project days in their class. Furthermore, the use of the eLearning platform by pupils and teachers is evaluated (i.e. what is the proportion of completed eLearning lessons).

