## Statistical methods

### Statistical methods for primary and secondary outcomes {20a}

For the primary outcome (i.e. reduction in victimization and perpetration rates in IG compared to CG; see first objective), three-level mixed effect regressions with the dependent variables bullying victims (yes/no) and perpetrators (yes/no) will be conducted. For secondary outcomes (i.e. reduction in psychological distress, self-harming behaviour, and problematic Internet use in IG compared to CG; see second objective), dependent variables will be scores of the KIDSCREEN-27, SDQ, self-harming behaviour, IGDS, and SMDS (grades 5 to 9) or the scores of the KIDSCREEN-10 (grades 3 and 4). The fixed effects are the factors group (IG, CG), measurement point (T0, T1, T2), and the interaction of both (group × measurement point). The hierarchical random effects are the factors school (level 3) and class (level 2). The analyses are conducted using Wald tests (interaction group × measurement point). In order to investigate the third objective (i.e. effectiveness of specific program components), a variable reflecting the implementation of a specific component of the program (assessed via teacher surveys as well as via eLearning utilization) is included as a covariate and as an interaction term with group, measurement point, and their triple interaction in the model. The triple interaction allows for the identification of the effectiveness of a specific program component. The analysis is repeated for different components. The fourth objective (i.e. individual characteristics predicting program success at the individual level) is investigated by adding a pupil level to the multilevel analysis. The association of surveys from different time points to pupils is ensured by individual codes. Codes with a Levenshtein distance not greater than 2 are assigned to the same pupil. For each individual characteristic (i.e. personality traits, internal self-blame, callous-unemotional traits), the model of objective one is extended by the characteristics at baseline as a predictor and a pupil specific random intercept. In order to compensate for the small number of randomized schools, we will apply a small sample error correction to each analysis using school-level bootstrap. All calculations are performed with a significance level of 0.05.

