### Methods in analysis to handle protocol non-adherence and any statistical methods to handle missing data {20c}

The analysis is an intention to treat analysis; whole schools were randomly assigned to the two conditions intervention group vs. control group. In order to enable sub-analyses differentiated by program dose, a score based on the intensity of the central program components will be created for each school.

Sensitivity analyses are done on the complete-case sample, i.e. excluding schools where measurement points are missing.

To deal with our fourth objective (individual characteristics predicting the program success at the individual level), the association of questionnaires from different time points to pupils is required. Therefore, individual codes with a Levenshtein distance not greater than 2 are assigned to the same pupil. Apart from this strategy to reduce missings, no missing data is imputed.

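### The analyst blinding is claimed for all statistical analyses, but it cannot hold for the component and dose analyses, because the T1 teacher survey exists only in intervention schools

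*Protocol article*

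**What the plan says.** All references are to the protocol article.

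- **Who will be blinded {17a}.** Schools and researchers are not masked. For the analysts: "The data analysts will be blinded to group allocation (dummy coded) when conducting the statistical analyses". No analysis is excepted.
- **Procedure for unblinding if needed {17b}.** "Since only data analysts are blinded, unblinding is not needed".
- **Plans for assessment and collection of outcomes {18a}.** Implementation is documented by an annual teacher survey, an "anonymous online survey (T1: only IG; T2: IG and CG").
- **Outcomes, Third objective.** Component effectiveness draws on teacher surveys at T1 and T2, and "the use of the eLearning platform is recorded continuously".
- **Statistical methods for primary and secondary outcomes {20a}.** For the third objective, the model gains a component variable. It "is included as a covariate and as an interaction term with group, measurement point, and their triple interaction in the model". Its values come from the teacher questionnaires and the platform records.
- **Handling of non-adherence and missing data {20c}.** For sub-analyses by dose, "a score based on the intensity of the central program components will be created for each school".

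**The concern.** After baseline, analyst blinding is the only masking this trial claims. Schools know their arm, researchers deliver the program, and pupils report the outcomes themselves. A reader of the final report will therefore give some weight to a statement that the analyses were done blind.

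Dummy coding hides the arm only while nothing else in the analyst's file varies by arm in a recognisable way. Implementation data do vary that way: at T1 one arm has teacher-survey records and the other has none by design. If the blinding sentence stays as it is, the report could describe the component and dose analyses as blinded when they were not. It would also leave unclear whether the primary analysis was finished before the code became readable.

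**Working it through.** No figure in the plan is at stake. The check is whether the stated sections can all hold together.

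**Step 1: what the blind consists of.** Group is a two-level variable with masked labels ({17a}), say A and B. To learn the arm of every school, an analyst needs only to learn whether A or B is the intervention.

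**Step 2: what the component model requires.** The third-objective model in {20a} contains group, measurement point, the component variable and their interactions. Each component value must sit beside a school and its group code. The survey is anonymous for the teacher, but the section on discontinuing or modifying interventions {11b} uses it to assess fidelity school by school, so the link to school is intended.

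**Step 3: what the linked data show.** Set the survey schedule in {18a} against the model:

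| Source | Intervention, T1 | Control, T1 | Basis |
|---|---|---|---|
| Teacher survey | invited | not invited | stated in {18a} |
| Program eLearning use before T1 | expected | none expected | inferred from the one-year delay in {6b} and {8} |
| Teacher survey, T2 | invited | invited | stated in {18a}; does not separate the arms by its presence |

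One T1 teacher record attached to a school coded A means that A is the intervention. All schools coded A are then known to be intervention and all coded B to be control: 20 + 20 = 40 on the planned split.

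**Step 4: does this depend on response?** Hardly. What matters is at least one T1 record in the whole intervention arm, not one in every school. As an assumed low case, take 5 invited teachers in each of 20 schools and an independent 10% response. The chance of at least one record is 1 − 0.9^(5 × 20) = 1 − 0.9^100 ≈ 0.99997. The documents give no teacher numbers or response rates, so this only illustrates the point.

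**Step 5: the dose score.** The section {20c} does not say which period the score covers. A score for the period to T1, or one built from the T1 records, reveals the code in the same way. A finished score covering only the period after T1 might not.

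**Step 6: the primary and secondary models.** In {20a} these use group, measurement point, their interaction, and random effects for school and class, with outcomes from the pupil survey. No teacher-survey, Moodle or dose variable enters. They can be run with the code intact if the implementation data are not yet linked.

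**The case against.** The strongest reply is that nothing shows the primary analysis to be compromised. Its model needs none of the revealing data. The pupil survey runs in LimeSurvey, eLearning use comes from Moodle, and the teacher survey is a separate instrument, so the data can be kept apart. This stands.

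A reader might go further and infer that arm knowledge would steer decisions ahead of the primary test. The documents do not support that:

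- Matching of pupil codes follows a fixed rule (Levenshtein distance of at most 2) and serves the fourth objective. The primary model has no pupil level.
- Schools with missing waves have a stated treatment in {20c}: intention to treat, a complete-case sensitivity analysis, and no imputation.
- No discretionary exclusion of surveys is described.

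A reader might also treat the absence of a fixed order of analyses as the fault. Order, locking and code-break dates are commonly left to a statistical analysis plan, which is not at hand, so that absence is not a finding. Nor do the documents say that all 20 intervention schools will have T1 teacher and eLearning data: participation in the survey is by invitation, schools may omit pupil eLearning, and primary pupils receive none. The decoding argument does not need that count.

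Finally, {17b} can be read as saying only that no pupil or school is masked, so no allocation need be revealed during the trial. That is a fair reading. It still leaves {17a} unqualified, and {17a} is the sentence that cannot hold for every planned analysis.

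**Conclusion.** The point holds in a limited form. The blinding statement in {17a} is too broad: the planned component analyses cannot be done by an analyst who is blind to group, and neither can dose analyses that use data from before T1. One linked T1 teacher record is enough to unmask every school.

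The conclusion rests on two statements in the plan: the T1 teacher survey is confined to the intervention arm, and its data enter a model together with group. The parallel argument from eLearning use rests on an inference, since the article does not say outright that control schools have no platform use before T1. The teacher survey is sufficient without it.

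Severity is minor. The component analyses are labelled exploratory in the Objectives and the dose analyses are sub-analyses. No bias in the primary or secondary results is shown, and none can be quantified from the document. What needs correcting is a claimed property that part of the planned analysis does not have.

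**What to change.** 1. In {17a}, limit the statement to the primary and secondary outcome models.
2. Run and freeze those models, code and output, on a pupil-survey file that carries only the dummy arm code and no teacher-survey, Moodle or dose variable.
3. In {17b}, replace the present sentence with a statement that linking the implementation data is the point of unblinding, with its date recorded.
4. Report the component and dose analyses as unblinded.

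The cost is one extra data export and a log entry. Data collection, models and sample size do not change. The step has to be in place before implementation data are first linked to the outcome file.

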### Procedure for unblinding if needed {17b}

Since only data analysts are blinded, unblinding is not needed.

## Data collection and management

### Plans for assessment and collection of outcomes {18a}

Pupils complete anonymous online self-report questionnaires created with LimeSurvey. The responsible teachers read standardized instructions to their pupils and every pupil receives a randomly assigned Login ID (random combination of numbers and letters) for registering on the start page of the survey. In the beginning of the survey, all pupils decide about their participation in the accompanying evaluation study. Approving pupils are asked to create an individual code to enable the association of repeated assessments to the same pupil and receive additional questions during the course of the survey. The assessments take place at school during regular class times and the duration is a maximum of 90 min. The first secondary schools conducted their baseline in March 2022. The first primary schools conducted their baseline in October 2023.

The following scales are used in primary as well as secondary schools:Demographics (2 items)Bullying Screening ( [28, 29]; 6 items)Bullying circumstances for victims, perpetrators, and bystanders based on the Olweus Bullying Questionnaire Revised (OBQ-R; [41]; maximum of 18 items for primary schools and maximum of 25 items for secondary schools, exact number depends on given answers in the Bullying Screening)KIDSCREEN-10 ( [30]; 10 items) for primary schools or KIDSCREEN-27 ( [31]; 27 items) for secondary schools:oKIDCREEN-10: Cronbach’s alpha = 0.82, test–retest reliability assessed by an intraclass correlation coefficient (*ICC*) = 0.70, and demonstrated validity [30]oKIDSCREEN-27: Test–retest reliability *ICC*s = 0.61–0.74 for the different dimensions and was found to be valid [31]

In secondary schools, the following scales are additionally used:Strengths and Difficulties Questionnaire (SDQ; [32]; 25 items): Mean Cronbach’s alpha = 0.73 and mean test–retest reliability after 4 to 6 months = 0.62Self-harming behaviour within the last 12 and 3 months based on the Self-Injurious Thoughts and Behaviours Interview (SITBI; [33]; 6 items)Internet Gaming Disorder Scale (IGDS; [34]; 11 items): Reliability coefficients of 0.82 and 0.83 [42]Social Media Disorder Scale (SMDS; [35]; 11 items): Reliability coefficient of 0.57Level of Personality Functioning Scale—Brief Form (LPFS-BF; [36]; 12 items): Cronbach’s alpha = 0.82 and promising construct validity

In secondary schools, pupils who agree to participate in the accompanying research also fill in:Attributions for Victimization Experiences Measure ( [37, 38]; 17 items): Cronbach’s alpha = 0.71–0.80 for the subscalesInventory of Callous-Unemotional Traits—Youth Version (ICU; [39]; 24 items): Cronbach’s alpha = 0.77

All measures are well tested standard instruments and have previously been used in adolescent samples.

In addition to the pupil survey, the evaluation of the program relies on documentation of the actual program components implemented at each school through an annual teacher survey. For this purpose, teachers receive an invitation to an anonymous online survey (T1: only IG; T2: IG and CG), taking a maximum of 5 min to answer. In the questionnaire, all teachers are asked to estimate the workload and the benefit of the program and get the opportunity to give feedback to the program. Class teachers are additionally asked about the amount of eLearning units, class meetings, and project days in their class. Furthermore, the use of the eLearning platform by pupils and teachers is evaluated (i.e. what is the proportion of completed eLearning lessons).

### Plans to promote participant retention and complete follow-up {18b}

Core team members regularly obtain trainings and coordinate and plan the implementation of the program components. This task also comprises the coordination of the baseline and follow-up surveys with their pupils including the coordination of additional assessment dates for previously absent pupils. The research team monitors the progress of the pupil survey and actively contacts the core teams in case of delays or low response rates.

### Data management {19}

Survey data are collected online via LimeSurvey and data on the use of the eLearning platform will be collected online via Moodle. Computerized assessments guarantee the highest level of data integrity and quality, i.e. missing data will be minimized and false data entry will be prevented. Furthermore, online access allows for continuous monitoring of data collection, documentation of access logs, and traceability of all entered data (user and timestamp) as well as restoration of all previous states. A Distributed Replicated Block Device (DRBD)-based cluster provides synchronous replication of all data during data entry on two separate servers and highest availability. The data are stored and processed in a way so that individuals can no longer be identified. No third parties will gain access to the original data. Full and incremental back-ups are conducted following a predefined back-up plan. All research data will be archived for 10 years after the study has ended.

### Confidentiality {27}

Survey and eLearning data will be stored via central servers based in Germany and processed in a way so that individuals cannot be identified. Regarding the pupil survey, the confidentiality of pupils is secured by providing random Login IDs and the creation of individual codes. Data storage and transfer is encrypted. Access to the data is strictly limited to authorized persons and is password-protected. All confidential information is subject to medical confidentiality and to the requirements of the *Landesdatenschutzgesetz Baden-Wuerttemberg, Bundesdatenschutzgesetz*, as well as the European Union General Data Protection Regulation.

### Plans for collection, laboratory evaluation, and storage of biological specimens for genetic or molecular analysis in this trial/future use {33}

No biological specimens will be collected in this trial.

## Statistical methods

### Statistical methods for primary and secondary outcomes {20a}

For the primary outcome (i.e. reduction in victimization and perpetration rates in IG compared to CG; see first objective), three-level mixed effect regressions with the dependent variables bullying victims (yes/no) and perpetrators (yes/no) will be conducted. For secondary outcomes (i.e. reduction in psychological distress, self-harming behaviour, and problematic Internet use in IG compared to CG; see second objective), dependent variables will be scores of the KIDSCREEN-27, SDQ, self-harming behaviour, IGDS, and SMDS (grades 5 to 9) or the scores of the KIDSCREEN-10 (grades 3 and 4). The fixed effects are the factors group (IG, CG), measurement point (T0, T1, T2), and the interaction of both (group × measurement point). The hierarchical random effects are the factors school (level 3) and class (level 2). The analyses are conducted using Wald tests (interaction group × measurement point). In order to investigate the third objective (i.e. effectiveness of specific program components), a variable reflecting the implementation of a specific component of the program (assessed via teacher surveys as well as via eLearning utilization) is included as a covariate and as an interaction term with group, measurement point, and their triple interaction in the model. The triple interaction allows for the identification of the effectiveness of a specific program component. The analysis is repeated for different components. The fourth objective (i.e. individual characteristics predicting program success at the individual level) is investigated by adding a pupil level to the multilevel analysis. The association of surveys from different time points to pupils is ensured by individual codes. Codes with a Levenshtein distance not greater than 2 are assigned to the same pupil. For each individual characteristic (i.e. personality traits, internal self-blame, callous-unemotional traits), the model of objective one is extended by the characteristics at baseline as a predictor and a pupil specific random intercept. In order to compensate for the small number of randomized schools, we will apply a small sample error correction to each analysis using school-level bootstrap. All calculations are performed with a significance level of 0.05.

We orientated our expected effects on the effects of school-bullying prevention programs reported by the latest meta-analyses [14], but would nevertheless consider even smaller program effects as clinically meaningful, first because of the strong causal relationship of bullying experiences with the development of mental disorders [6–9], and second because of the resulting health care costs associated with bullying [43]. Given that this program aims at universal prevention of bullying and associated consequences for mental health, even small effects (i.e. slight changes in mean scores of mental health) can make meaningful contributions to prevalence rates and burden of disease [44].

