## Objectives {7}

The primary aim of this CRT is to evaluate the effectiveness of the newly developed school-based blended-intervention bullying prevention program *Bullying&You*. We aim to investigate whether *Bullying&You* leads to a reduction in victimization and perpetration rates among pupils in the intervention group (IG) compared to a waiting control group (CG) within 1 year (T1) and 2 years (T2), respectively (primary objective). Secondary aims are to explore whether the program leads to a reduction in psychological distress, self-harming behaviour, and problematic Internet use in the IG compared to the CG (second objective). In addition, exploratory analyses will aim to evaluate which specific components of the program are particularly effective in reducing bullying (third objective), and which characteristics of pupils predict program success at the individual level (fourth objective).

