### Outcomes {12}

#### First objective

The primary outcome of this trial is the reduction of bullying (prevalence of victims and perpetrators of direct, indirect, and cyberbullying within the last 6 months) assessed by the Bullying Screening [28, 29] from baseline (T0) to two annual follow-ups (T1 and T2) in the IG compared to the CG.

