### Sample size {14}

To estimate the required sample size, Monte Carlo simulations were carried out using Stata 16.1 with the following assumptions: Two measurement points of 15 secondary schools per group with 10 classes per school and 5 primary schools per group with 4 classes per school are expected to take part in the study. In each class, 25 pupils are expected. Baseline bullying prevalence is estimated to be 15%, and the intervention is expected to lead to a relative reduction in bullying of 25%. The standard deviation (*SD*) of bullying rates between schools is *SD* = 0.2 on the logit scale; the *SD* of classes within schools is *SD* = 0.4 on the logit scale. This leads to an intraclass correlation coefficient on the school level of 0.011 and 0.057 on the class level. The assumptions were chosen so that the simulated data corresponded to the data from the OBPP study [18]. With these assumptions, 1000 data sets were simulated and analysed by three-level mixed logistic regression with group, measurement point, and their interaction as fixed effects and random intercepts on the school (level 3) and class (level 2) level. Using an alpha-error probability of 0.05, with 40 schools and 8500 pupils (4250 IG and 4250 CG) the power would be 86%.

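### Victimization and perpetration are both tested as the primary outcome at 0.05 with no rule joining them: if either suffices, the false-claim risk is about 7% to 9.75%; if both are required, the 86% power is too high

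*Protocol article*

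**What the plan says.** Outcomes {12}, First objective, gives one primary outcome, the reduction of bullying, and defines it as "prevalence of victims and perpetrators of direct, indirect, and cyberbullying within the last 6 months". Objectives {7} puts victimization and perpetration rates side by side as the primary objective.

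Statistical methods {20a} turns this into two analyses: "three-level mixed effect regressions with the dependent variables bullying victims (yes/no) and perpetrators (yes/no) will be conducted". The test is described as follows: "The analyses are conducted using Wald tests (interaction group × measurement point"). The section closes its description with "All calculations are performed with a significance level of 0.05".

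Sample size {14} works with one bullying rate: 15% at baseline, a 25% relative reduction, alpha 0.05, 40 schools and 8500 pupils, and a power of 86%.

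On timing, the Methods part of the Abstract places the main endpoint at 1 year (T1). Objectives {7} and Outcomes {12} name both T1 and T2.

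**The concern.** Two primary regressions, each judged at 0.05, need a sentence that says what counts as success for the trial. The protocol has none. It does not say that either outcome is enough, that both are required, or that one is tested before the other.

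The choice matters in both directions. If one significant result is enough, the error rate of the primary claim is above the nominal 5%. If both are needed, the error rate is held, but the stated power describes one test and not the joint event. While the rule stays open, it can be chosen after the results are known. The effectiveness claim, on which wider dissemination of the program is said to depend, then has no defined error rate.

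**Working it through.** **Inputs from the protocol.** Two primary dependent variables and 0.05 per test ({20a}). From {14}: 15% baseline prevalence; 25% relative reduction, so 0.15 × 0.75 = 11.25%; SD 0.2 (school) and 0.4 (class) on the logit scale; per arm 15 × 10 + 5 × 4 = 170 classes of 25 pupils, so 4250 pupils.

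**Assumptions.** Two-sided tests, because sidedness is not stated. The correlation ρ between the two test statistics is not given, so it is varied from 0 to 0.9.

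**Step 1: reproduce the plan's figures.** Total pupils: 2 × 4250 = 8500. Intraclass correlations: 0.04/(0.04 + 0.16 + π²/3) = 0.011 and 0.20/(0.20 + π²/3) = 0.057. Both match.

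For power, the log odds ratio for 15% to 11.25% is −0.331. With class effects taken as independent at each measurement point, the variance of the interaction is

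3/(4250 × 0.15 × 0.85) + 1/(4250 × 0.1125 × 0.8875) + 4 × 0.16/170 = 0.00554 + 0.00236 + 0.00376 = 0.01166.

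The standard error is 0.108, the ratio is 0.331/0.108 = 3.06, and power is Φ(3.06 − 1.96) = 86.5%. The stated 86% is therefore reproduced for **one** outcome at two-sided 0.05. With class effects shared over time the same formula gives 96.1%, so the match rests on the independent-class variant.

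**Step 2: either outcome suffices.** The chance of at least one false significant result, when neither outcome is affected, is 1 − P(|Z₁| < 1.96 and |Z₂| < 1.96). At ρ = 0 this is 1 − 0.95² = 9.75%.

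**Step 3: both outcomes required.** The false-claim rate cannot exceed 5%. If each outcome has 86% power, joint power is P(Z₁ < 1.08 and Z₂ < 1.08), where Φ(1.08) = 0.86. At ρ = 0 this is 0.86² = 74.0%.

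| ρ | False claim if either suffices | Power if both required (86% each) |
|---|---|---|
| 0 | 9.75% | 74% |
| 0.3 | 9.5% | 76% |
| 0.5 | 9.1% | 77% |
| 0.7 | 8.3% | 79% |
| 0.9 | 7.0% | 82% |

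**Step 4: does the form of the test matter?** With T0, T1 and T2 in one model, the interaction can be a single test with 2 degrees of freedom per outcome. The either-suffices error is then 9.8%, 9.5%, 9.2% and 8.4% at ρ = 0, 0.3, 0.5 and 0.7, so the picture is the same. Counting only false claims of benefit, the rate is 4.9% at ρ = 0 and 4.5% at ρ = 0.5, against 2.5% for one test.

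**The case against.** The strongest reply is that the protocol never says that one significant result is enough. Its wording joins victims and perpetrators with an *and* throughout, which fits a both-must-succeed rule, and under that rule nothing is inflated. The 0.05 sentence is a per-test level and is compatible with that rule or with a fixed sequence. A testing order is also often left to the analysis plan, which is not shown.

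Much of this stands, and it limits the point. A reader might infer that the trial's error rate simply is 9% to 10%. The protocol does not support that: the figure applies only to the either-suffices reading, and it falls below 9% once the correlation exceeds about 0.53. High correlation is plausible, since both outcomes come from the same short screening instrument and the same schools.

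Two larger figures might also be inferred. About 16% to 17% would apply if T1 and T2 were tested separately for both outcomes. About 22% would apply if direct, indirect and cyberbullying were each tested in both roles. Section {20a} states neither: it lists two yes/no variables and an interaction that can be one joint test. Nor is the power calculation unrelated to the analysis. It models one regression of the planned kind, and if either outcome suffices and each meets the assumptions, 86% is a lower bound.

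The reply does not remove the gap. The protocol fixes two primary tests and a level for each, and these do not define a primary claim with 5% error. Under the conjunctive reading the power statement fails instead.

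**Conclusion.** The point holds in conditional form. With two primary regressions at 0.05 each and no joining rule, one of two things is off. Either the false-claim risk is about 7% to 9.75% instead of 5%, or the 86% overstates the power for success, which would be about 74% to 82%.

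Both ranges assume two-sided tests and a correlation between the tests of 0 to 0.9. The power range also assumes that each outcome separately reaches 86%, which means that the 15% prevalence and the 25% reduction apply to victims and to perpetrators alike. The protocol does not say which reading is intended, so neither range can be called the trial's actual figure.

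**What to change.** Before the analysis, add one decision rule to Statistical methods {20a} for the 1-year endpoint that the Abstract names as main. Either of these would do:

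- **Fixed sequence.** Test one outcome first at two-sided 0.05, and the other at 0.05 only if the first is significant. Victimization could come first, but that is only an example. The protocol does not rank the two, so the investigators must choose.
- **Both required.** Declare success only if both are significant at 0.05, and restate the power in Sample size {14} for joint success.

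In the same edit, state whether T2 comes later in the sequence or is secondary, so that the Abstract, Objectives {7} and Outcomes {12} agree. State also that the direct, indirect and cyber forms are reported descriptively.

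This needs no further schools or data. It takes a few sentences, plus the amendment and registry update that the protocol foresees for relevant changes. The fixed sequence costs the first test no power but makes the claim on the second outcome conditional. The both-required rule lowers the stated power. An equal split of alpha (0.025 each) would also hold the error at 5%, but by the Step 1 formula power per outcome would fall from 86.5% to 79.5%.
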